# A study protocol for a clustered randomised controlled trial to evaluate the effectiveness of a peer-led school-based walking intervention on adolescent girls’ physical activity: the Walking In ScHools (WISH) study

**DOI:** 10.1186/s12889-020-08600-0

**Published:** 2020-04-21

**Keywords:** Physical activity, Adolescent girls, Walking, Schools, Intervention

## Abstract

**Background:**

Adolescent girls in the UK and Ireland are failing to meet current physical activity guidelines. Physical activity behaviours track from childhood to adulthood and it is important that adolescent girls are provided with opportunities to be physically active. Walking has been a central focus for physical activity promotion in adults and may effectively increase physical activity levels among younger people. Following on from a pilot feasibility trial, the purpose of this cluster randomised controlled trial (c-RCT) is to evaluate the effectiveness of a novel, low-cost, peer-led school-based walking intervention delivered across the school year at increasing physical activity levels of adolescent girls.

**Methods:**

The Walking In ScHools (WISH) Study is a school-based c-RCT conducted with girls aged 12–14 years from eighteen schools across the Border Region of Ireland / Northern Ireland. Following baseline data collection, schools will be randomly allocated to intervention or control group. In intervention schools, female pupils aged 15–18 years will be invited to train as walk leaders and will lead younger pupils in 10–15 min walks before school, at break and lunch recess. All walks will take place in school grounds and pupils will be encouraged to participate in as many walks as possible each week. The intervention will be delivered for the whole school year (minimum 20–22 weeks). The primary outcome measure is accelerometer-measured total physical activity (counts per minute) (end of intervention). Secondary outcomes will include time spent in sedentary behaviour, light, moderate and vigorous intensity physical activity, anthropometry measures, social media usage and sleep. A mixed-methods process evaluation will also be undertaken.

**Discussion:**

The WISH Study will examine the effectiveness of a low-cost, school-based, peer-led walking intervention in increasing physical activity in adolescent girls when delivered across the school year. If the intervention increases physical activity, it would benefit adolescent girls in the defined target area with potential for wider adoption by schools across the UK and Ireland.

**Trial registration:**

ISRCTN; ISRCTN12847782; Registered 2nd July 2019.

## Background

Regular physical activity is associated with physiological and mental health benefits for adolescents including a reduced risk of obesity, improved fitness and cardiometabolic health, increased muscle and bone strength [1–3]. Despite this, globally, many children fail to meet current guidelines of 60 min of moderate-to-vigorous physical activity (MVPA) per day [4–6] and it is estimated that on the island of Ireland only 14% of post-primary school children meet the current recommendations [7]. Physical activity levels decline as children move into adolescence [8] and through to adulthood [7]. This decline is most pronounced among adolescent girls [9] where the average annual reduction in total physical activity from the age of 5 to 18 years is 4.6% [10]. Importantly, physical activity habits adopted during adolescence track into adulthood [11, 12] and may affect the likelihood of developing many chronic health conditions.

Schools are an excellent setting for physical activity promotion among adolescents [13] particularly as children spend 40% of their waking time at school [14], however, there is a lack of consensus on how best to promote physical activity within the school setting to ensure the maintenance of physical activity behaviours into late adolescence, and adulthood [13]. School-based Physical Education (PE) provides an opportunity for young people to participate in structured, regular physical activity [15] but research has shown that girls are offered significantly less PE time than boys [16]. In addition, extra-curricular physical activity within the school environment often reflects the content of the PE curriculum, i.e. team-based, structured sports [17] and girls are less likely to participate in such activities [18]. School recess may provide an opportunity to promote physical activity. Interventions during recess are feasible [19, 20] and female pupils tend to socialise with friends during this time but are less active than males so this period may provide a unique opportunity to increase physical activity levels in adolescent females [21–24].

Walking is the most natural form of physical activity [25] and has been recommended for the promotion of public health [26, 27]. Walking addresses many of the reported barriers to physical activity, such as lack of time, money or poor health [28] and is the most popular form of physical activity for adult women with over 50% walking for recreation each week [29]. A recent meta-analysis has demonstrated the beneficial effects of walking interventions on adult health [30], however less is understood about the potential of walking to promote physical activity in adolescents. The results of a recent systematic review outlined that walking interventions may provide an effective means for increasing walking in younger populations, at least in the short term but called for additional research into walking and physical activity in adolescents [31]. There is also evidence that walking has benefits for mental health, wellbeing and sleep quality [32, 33] but the evidence in the adolescent population is limited.

It is recognised that there are many barriers to participation in physical activity among adolescent girls including a perceived lack of time, peer pressure, negative school experiences, social media and lack of confidence [34–36]. Focus group discussions with adolescent girls have highlighted the characteristics of a school-based intervention acceptable to pupils to encourage participation among low active girls [37]. This work suggested activities that required no change of uniform and could be performed with friends, during the school day, were likely to be accepted and encourage participation [37]. It is recognised that enjoyment of physical activity is positively correlated with physical activity participation levels for adolescents [38] and research has shown that low-active girls enjoy non-competitive physical activity within the school setting and enjoy physical activity when participating with friends [39]. Research has shown that friends engage in similar levels of physical activity and physical activity interventions within the peer group may be effective as friendship can influences physical activity behaviour [40]. Furthermore, peer leadership is a promising strategy for influencing adolescent behaviour and increasing physical activity as peer leaders can motivate pupils to initiate and sustain behaviour change [41, 42].

Declining physical activity levels during adolescence may be attributable to various other factors including intrapersonal (e.g., self-efficacy, perceived competence, self-image), social (e.g., peer influence) and environmental factors (e.g., gender-relevant physical activity opportunities) [43]. It appears that during adolescence there is a lack of interest in the activities offered [44], girls are less likely to engage in organised sport [45] and there is a need to provide physical activity opportunities for those discouraged by the competitive selection process [46] which may increase physical activity in adolescent girls [44, 47]. Considering there is growing pressure on schools to improve academic standards and performance, there is a need for physical activity interventions to be delivered at school but outside of curriculum time [48] and in recent years, there has been growing interest in the promotion of physical activity during school recess [49]. As girls are less active during recess [22, 23, 49], this period may present an opportunity to promote physical activity. However, despite the potential of school recess to promote physical activity, there is a lack of intervention research in adolescent girls [19] and given the imperative to increase physical activity in adolescent girls, finding effective, sustainable, low-cost interventions is essential.

The aim of this cluster-randomised controlled trial is to evaluate the effectiveness of a novel, low-cost, peer-led school-based walking intervention, delivered across the school year, at increasing accelerometer-measured physical activity levels of adolescent girls. It is hypothesised that intervention pupils will increase daily physical activity and replace sedentary behaviour during the school day with walking.

## Methods

### Study design

The WISH study is a school-based clustered randomised controlled trial (c-RCT). The design of the project was informed by a feasibility pilot study [50] that used the Medical Research Council (MRC) [51] framework for complex interventions to develop a peer-led walking intervention. Specifically, following a systematic review of walking interventions in children and adolescents [31], focus groups were conducted to explore the attitudes of adolescents towards physical activity [37]. The findings of both the systematic review and focus groups were used to inform the design of the peer-led, school-based walking intervention [50] based on the socioecological framework and informed by Self-Determination Theory (SDT), which provides a framework for understanding and enhancing the motivational mediators of behaviour change [52–54].

Eighteen post-primary schools will be recruited across the Border Region of Ireland / Northern Ireland. Following completion of baseline data collection, schools will be randomised using a 1:1 allocation. Study outcomes will be assessed at four timepoints: baseline (T0), mid-intervention (T1), end of intervention (T2) and follow up (T3) as outlined in Fig. 1. A mixed-methods process evaluation will be undertaken at baseline and at the end of the intervention. Table 1 provides an overview of data collection and outcome measures, the details of which are provided below.

**Fig. 1 Fig1:**
[figure not shown]
Study Flow Chart

**Table 1 Tab1:** WISH Study Data Collection and Outcome Measures

Outcome measure	Baseline (T0)	Mid-intervention (T1)	End of intervention (T2)	13-month follow-up (T3)
Demographic information (age, postcode/Eircode)	X			
Total physical activity (accelerometery)	X	X	X	X
Time spent in sedentary behaviour, and low, moderate and vigorous intensity physical activity (accelerometery)	X	X	X	X
Proportion of pupils meeting current physical activity recommendations (accelerometery)	X	X	X	X
BMI z-scores (height and weight)	X		X	X
Waist: hip ratio (waist and hip circumference)	X		X	X
Coping, resilience and cognitive reappraisal (Emotion Regulation Questionnaire for Children) [55]	X		X	X
Sleep quality, duration and efficiency (Pittsburgh Sleep Quality Index) [56]	X		X	X
Social media use, social integration and emotional connection to social media [57, 58]	X		X	X
Body weight and appearance satisfaction [59]	X		X	X
Self-efficacy for physical activity and walking [60]	X		X	X
Health-related quality of life (Kidscreen-10) [61]	X		X	X
Reasons for engaging in physical activity (BREQ-3) [62, 63]	X		X	X
Friendship nominations	X		X	
Process evaluation: focus groups with all pupils (control & intervention)	X			
Process evaluation: focus groups with intervention pupils			X	
Process evaluation: walk leaders - perception of physical activity and fitness [64], physical activity self-efficacy [65], physical activity enjoyment [66] and leadership skills [67]	X		X	
Process evaluation: interviews with walk leaders			X	
Process evaluation: interviews with teachers			X	

*Abbreviations*: *BMI* Body Mass Index

### Recruitment

#### School recruitment

The study setting will be post-primary schools in the Border Region of Ireland / Northern Ireland. Using school enrolment data [68, 69], schools that meet the following criteria will be invited to participate:
Northern Ireland: Schools that have at least 80 girls across years 9–10 and located in Co. Derry/LondonderryIreland: Schools in Co. Donegal with an enrolment of > 240 girls

Invitation letters accompanied with an expression of interest form will be sent to school principals. Where requested, a member of the research team will visit the school to provide a short overview of the trial for relevant staff. We aim to recruit 18 schools, of which 9 will be randomly allocated to intervention arm with the other 9 allocated to the control arm. Within each school, at least 24 children will be recruited (i.e., minimum of 432 children in total). Should it not be possible to recruit eighteen schools in the selected counties, schools that meet the inclusion criteria (Northern Ireland: at least 80 girls across years 9–10; Ireland: enrolment of > 240 girls) from other counties across the Border Region of Ireland / Northern Ireland will be invited to participate.

#### Participant recruitment

Following permission from the school principal, female pupils in Year 9/10 (Northern Ireland) and 1st/2nd year (Ireland) will be invited to take part in the study via a presentation from the study team which will inform pupils about the study, the randomisation process and intervention. In schools with < 70 female pupils in either Year 9/10 (Northern Ireland) or 1st/2nd year (Ireland), all girls in that cohort will be invited to participate. For the larger schools (> 70 pupils in either Year 9/10 (Northern Ireland) or 1st/2nd year (Ireland)), each school will be asked to provide a list of the form classes within Year 9/10 (Northern Ireland) or 1st/2nd year (Ireland) and for those schools with mixed ability form classes, classes will be randomly selected to attend the recruitment presentation. If pupils are grouped into form classes based on academic ability, we will randomly invite equal numbers of classes from each band (for example, top, middle and bottom) to attend the recruitment presentation. At a minimum, all potential pupils (and parents/guardians) will be provided with a copy of the participant information sheet. Parents/guardians will be asked to provide written consent. Written assent will be obtained from pupils. The study exclusion criteria are outlined below:
Male pupils are not eligible for inclusion in this study, as it seeks to assess the effectiveness of a walking intervention targeted at adolescent girls only.Pupils who are unable to walk or for whom walking is contraindicated will not be eligible for inclusion as taking part in increased physical activity during the school day may not be suitable for this population.

In intervention schools, female pupils aged 15–18 years will be identified by staff and invited to train as walk leaders, lead the walks and participate in an interview at the end of the intervention. One staff contact per intervention school will be recruited for an interview at the end of the intervention and written informed consent will be obtained. Walk leaders will be provided with a participant information sheet and will provide written informed consent. Participants will be free to withdraw from the study at any point without giving reason. This study was approved by Ulster University Research Ethics Committee (Ref: REC/19/0020) on 21.06.2019.

### Sample size calculations

Sample size calculations are based on the WISH feasibility trial [50], which detected a mean difference of 11.41 min in total physical activity (light, moderate and vigorous intensity physical activity) measured using accelerometery between the intervention (2 schools consisting of a total of 79 children) and control (4 schools consisting of 84 children in total) groups. In order to detect a difference of 11.41 min total physical activity per day between groups, assuming a standard deviation (SD) (pooled intervention and control group SD) of 25 min in total physical activity, a power of 80%, a significance of 0.05, an average cluster size of 20 children, an intra-class correlation of 0.03 (calculated from pilot data [50]), and a coefficient of variation of 0.46, the sample size needed is 15 schools increasing to 16 schools (8 per study arm) to allow for 10% cluster attrition. To allow for 20% loss to follow up we will recruit at least 24 children per cluster (at least 384 children in total). Based on recruitment rates of 34% in our feasibility study [50], all schools that have at least 80 girls across years 9–10 (Northern Ireland) or total enrolment of > 240 girls (Ireland) will be eligible to participate in the study. From the Northern Ireland School Census [68] we estimate that 77 schools meet these criteria and based on 2016 school recruitment data for Ireland [69] 54 post-primary schools meet these criteria.

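### Both attrition allowances in the sample size section fall short of the losses they are meant to cover, and the resulting 16 schools and 384 pupils are never linked to the 18 schools and 432 pupils actually planned

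*Protocol article*

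**What the plan says.** The section on sample size calculations in the protocol article sets out to detect a difference of 11.41 minutes per day with an SD of 25 minutes, "a power of 80%, a significance of 0.05, an average cluster size of 20 children", an intra-class correlation of 0.03 and a coefficient of variation of 0.46. It concludes that "the sample size needed is 15 schools increasing to 16 schools (8 per study arm) to allow for 10% cluster attrition". On pupils it adds: "To allow for 20% loss to follow up we will recruit at least 24 children per cluster (at least 384 children in total").

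The section on school recruitment gives other figures: "We aim to recruit 18 schools, of which 9 will be randomly allocated to intervention arm", with 9 for control, and "Within each school, at least 24 children will be recruited (i.e., minimum of 432 children in total"). The abstract and the study design section also give eighteen schools, and the randomisation section allocates 9 to each arm. Nowhere does the article explain the step from 16 to 18.

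**The concern.** An allowance for attrition should leave the required number after the assumed loss, so the requirement is divided by the proportion retained. Neither figure in the sample size section passes that test. The number of schools given as sufficient drops below the stated requirement once the stated loss occurs, and so does the number of pupils per school.

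At stake is the reliability of the stated justification. The section that should support the trial's size supports a smaller one (8 schools per arm, 384 pupils) than the one planned (9 per arm, 432), and it does so with faulty arithmetic. A reader using that section to judge what number of schools is enough would take 16 as adequate for 80% power with the losses already covered. The pupil figure also reaches the operative plan, because the recruitment section uses the same 24 per school.

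**Working it through.** **Inputs, all from the sample size section.** Difference d = 11.41 min/day; SD = 25 min; power 80%; alpha 0.05; average cluster size m = 20; ICC = 0.03; CV = 0.46; cluster attrition 10%; pupil loss 20%. The section does not state sidedness, what the CV refers to, or the method. I assume a two-sided test and take the CV as variation in cluster size.

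**1. Reproducing the stated 15 schools**

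- Unadjusted size per arm: 2 × (1.960 + 0.842)² × (25/11.41)² = 75.4.
- Design effect: 1 + ((1 + CV²)m − 1) × ICC = 1 + ((1 + 0.2116) × 20 − 1) × 0.03 = 1.697.
- Adjusted size per arm: 75.4 × 1.697 = 127.9, or 127.9/20 = 6.39 schools per arm. That is 12.8 schools in total by the normal approximation, which is not 15.
- Noncentral t on (schools − 2) degrees of freedom: 15 schools of 20 give 80.1% power with the arms treated as equal (7.5 each), or 79.9% with a 7/8 split. Fourteen schools give 76.8%.

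So the stated 15 is reproduced by the t-based calculation and not by the normal approximation.

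**2. School allowance (10%)**

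- Retained from 16: 16 × 0.9 = 14.4, below 15. Losing one school of 16 is 1/16 = 6.25%.
- Needed: 15/0.9 = 16.7, so 17, or 18 for equal arms.
- The common shortcut of multiplying does not give 16 either: 15 × 1.1 = 16.5, which also rounds up to 17.

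**3. Pupil allowance (20%)**

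- Retained from 24: 24 × 0.8 = 19.2, below 20.
- Needed: 20/0.8 = 25.
- The stated 24 equals 20 × 1.2, so the loss was apparently added to the requirement and not divided out.

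**4. Totals**

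16 × 24 = 384 and 18 × 24 = 432. Each product is correct; what differs is the number of schools behind it.

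**5. Power after the stated losses**

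At m = 19.2 the design effect is 1 + (1.2116 × 19.2 − 1) × 0.03 = 1.668.

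| Recruited | Retained | t-based | Normal |
|---|---|---|---|
| 16 × 24 | 14.4 schools of 19.2 | 77.2% | 83.6% |
| 16 × 24 | 14 whole schools of 19.2 | 75.8% | 82.6% |
| 18 × 24 | 16.2 schools of 19.2 | 82.6% | 87.6% |
| 18 × 24 | 16 whole schools of 19.2 | 82.1% | 87.2% |

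The pupil error alone is small: by the t-based method, 15 schools of 19.2 give 79.2%, against 80.1% for 15 schools of 20.

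**The case against.** The strongest reply is that the operative design absorbs both errors. Eighteen schools is the correctly inflated, even number, and it appears everywhere except the sample size section. If the selected counties cannot supply 18 schools, the recruitment section extends invitations to other counties in the Border Region. The sample size section estimates 77 and 54 eligible schools in the two jurisdictions. Nothing permits stopping at 16, and 24 pupils is a floor, not a cap. This stands, and it limits the point to the justification.

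A reader might infer that the article contradicts itself on the size of the trial. It does not, strictly. The 384 is worded as a minimum, and a target of 432 lies above it. What remains is two different minima, and two different numbers per arm, with no link between them.

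A reader might also infer that the trial will miss 80% power. The documents do not support that for the planned 18 schools under either method. Even for 16 schools, the shortfall appears only with the t-based method, which the article does not name. With the normal approximation, power stays above 80%.

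Finally, 16 could have come from an unrounded requirement of 14.4 or less, since 14.4/0.9 = 16. The article shows no such figure. It states 15 and inflates from there, so the sentence is wrong as written whatever lies behind it.

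**Conclusion.** The point holds as an arithmetic and reporting error. From the section's own 15 schools and 20 pupils, 16 schools do not cover 10% cluster loss and 24 pupils do not cover 20% pupil loss. This part needs no assumption about method. The gap between 16/384 and 18/432 is an unexplained mismatch.

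The effect on power depends on two-sided alpha of 0.05, on the CV being cluster-size variation, and on the method. For 16 schools of 24 after the stated losses it is about 76–77% (t-based) or 83–84% (normal). For the planned 18 schools of 24 it is about 82–83% or 87–88%. The t-based figures deserve more weight because that method reproduces the stated 15, but this is an inference. The planned trial keeps its 80% power, so severity is moderate to minor.

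**What to change.** In the sample size section, state that 15 schools are needed, that 10% cluster attrition raises this to 17, and that equal arms round it to 18 (9 per arm). Replace 16 schools and 384 pupils with 18 and 432, so that the section agrees with those on recruitment and randomisation.

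For pupils, choose one of two statements:

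- Keep 24 per school, say that this leaves about 19 after 20% loss, and give the resulting power with the method used. On the assumptions above it is about 82–83% by the t-based calculation; the trial statistician should confirm this against the original calculation.
- If 20 retained pupils per school is a requirement, state 25 per school, which is 18 × 25 = 450 in total.

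Name the sidedness of the test, the meaning of the CV and the calculation method in the same sentence, so that the 15 can be checked. The first option costs only restated figures, since 18 schools and 432 pupils are already planned. The second adds one pupil per school, 18 in all.
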